### Statistics

2.8.

All data obtained in this study will be analyzed using SPSS 25.0 (SPSS Inc., Chicago, IL, USA). The analysis will be conducted using the Intention-to-Treat (ITT) analysis approach. Continuous data that conform to a normal distribution will be described using the mean ± standard deviation; otherwise, the median (interquartile range) [Median (Inter Quartile Range), M(IQR)] will be used. Categorical data will be analyzed and described using frequencies. The specific analysis is as follows.

#### Baseline data

2.8.1.

To ensure comparability between the two groups prior to the intervention, we will compare differences in each outcome between the two groups at baseline. The t-test, non-parametric test, or chi-square test will be employed to compare the general demographic data, primary and secondary outcomes, and plasma TMAO levels between the two groups. Data will be analyzed using two-sided tests, with a significance level of α = 0.05. A *p* value of <0.05 indicates a statistically significant difference.

#### Clinical observation outcomes

2.8.2.

Missing values will be imputed using multiple imputation methods. Linear mixed models will be used to analyze data from the four measurement time points to compare group effects, time effects, and interaction effects on outcome indicators between the two groups. The model will include group, time, and the group × time interaction as fixed effects, with the subject set as a random intercept to account for the inherent correlation in repeated-measure data. The model will include variables that were unbalanced between groups at baseline as covariates to correct for the impact of baseline differences on treatment effect estimates and ensure the robustness of the results. If a significant interaction is detected, the Bonferroni corrections post-hoc test will be employed to further determine its significance, with the significance level set at *p* < 0.05 for a two-tailed test.

Given that the inclusion criteria of this study do not restrict cognition and emotional state, the study may be insufficiently sensitive to detecting improvements induced by the intervention. Based on this, we will conduct subgroup analyses focusing on subgroups with mild cognitive impairment (MoCA score < 26), depressive symptoms (HAMD score > 7), and anxious symptoms (HAMA score > 7), respectively. We will analyze the impact of the intervention on cognitive and emotional scores separately within these subgroups to further identify the populations that benefit from the intervention and to more comprehensively evaluate the potential benefits of the intervention.

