#### Sham IM group

2.4.2.

Participants in the control group will receive sham far-infrared moxibustion intervention. The treatment protocol will be identical to that of the treatment group, except that the device will not emit infrared rays when turned on.

In addition, both groups of participants will receive therapeutic lifestyle changes, including a balanced diet, moderate increase in physical activity, weight control, smoking cessation, and limited alcohol consumption.

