### Outcomes

2.5.

Professional assessors will observe primary and secondary outcomes in participants at four time points: baseline (T1), after 4 weeks of treatment (T2), after 8 weeks of treatment (T3), and 4 weeks after the end of treatment (T4) (Table 1). To ensure the quality of scale assessments and minimize inter-rater variability, assessors will undergo unified standardized training based on a pre-established operation manual before the study begins. Only after passing the training will, they be allowed to perform assessments. Each scale assessor will be responsible for only part of the assessment tasks and will be unaware of the participants’ group assignments. They will also not be involved in the intervention process or the final data statistical analysis.

**Table 1. t0001:** Trial implementation schedule.

	Study period					
	Enrollment	Allocation	Treatment phase			Follow-up
Timepoint	−1 week		0 day	4 week	8 week	12 week

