#### Primary outcomes

2.5.1.

The change in LDL-C from baseline to 8 weeks after intervention.

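### The only stated correlation term is a random intercept, so the standard error and interval for the week-8 LDL-C change rest on compound symmetry and can be too small or too large

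*Protocol article*

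**What the plan says.** The primary outcome (section 2.5.1) is "The change in LDL-C from baseline to 8 weeks after intervention". Section 2.5 places the visits at baseline (T1), week 4 (T2), week 8 (T3) and four weeks after treatment ends (T4), so the primary contrast is T3 minus T1.

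Section 2.8.2 gives the analysis: "Linear mixed models will be used to analyze data from the four measurement time points". On the mean structure it says "The model will include group, time, and the group × time interaction as fixed effects", and on the correlation, "with the subject set as a random intercept to account for the inherent correlation in repeated-measure data". It states no residual covariance structure, robust standard error or degrees-of-freedom method.

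The week-8 comparison is reached through a gate: "If a significant interaction is detected, the Bonferroni corrections post-hoc test will be employed to further determine its significance". The test level given there is 0.05, two-sided.

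**The concern.** A random intercept with independent residuals is compound symmetry: one variance for every visit and one correlation for every pair of visits, whether 4 or 12 weeks apart. The error for the T1-T3 change is then an average over all six pairs, not the variance of that particular change.

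The design gives reason to doubt equal correlation. T1 precedes the device and also the lifestyle programme (section 2.4.2: "both groups of participants will receive therapeutic lifestyle changes, including a balanced diet, moderate increase in physical activity, weight control"). T2 and T3 are on treatment, and T4 is off it. If patients differ in how far they respond, or lipids drift over 12 weeks, T1 may correlate less with T3 than the follow-up visits do with one another. The pooled error would then understate the variance of the primary change. If T4 is the odd visit out, the error goes the other way.

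At stake is the calibration of the primary interval and p-value. The other outcomes measured at all four visits (TG, TC, HDL-C, MoCA, HAMD, HAMA, PSQI) are affected in the same way.

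**Working it through.** **Inputs.** From the article: four visits, 1:1 allocation, two-sided 0.05, 66 per group before and 79 after the dropout allowance. The article gives no LDL-C variances or correlations over time, so every pattern below is an assumption. The only error rate it gives is the nominal 5%.

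**Formula.** With complete, balanced data the random-intercept model equals a split-plot ANOVA. Its squared standard error for the T3-T1 group contrast uses the mean of the six pairwise-difference variances. Let r = Var(T3-T1) / that mean. The actual two-sided rate of an ungated, unadjusted test is 2 × [1 - Φ(1.96/√r)].

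With SD 1 and correlation ρ, a pair has difference variance 2(1-ρ). For serial correlation 0.7 per 4 weeks:
- lag 1: 2(1-0.7) = 0.60, three pairs
- lag 2: 2(1-0.49) = 1.02, two pairs
- lag 3: 2(1-0.343) = 1.314, one pair
- mean = (1.80 + 2.04 + 1.314)/6 = 0.859, so r = 1.02/0.859 = 1.19 and the rate is 7.2%.

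In the table, "a/b" means baseline-to-follow-up correlation a and follow-up-to-follow-up correlation b.

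| Assumed pattern | Var(T3-T1) | Mean of six | r | Rate |
|---|---|---|---|---|
| Compound symmetry 0.7 | 0.60 | 0.60 | 1.00 | 5.0% |
| Serial 0.7 | 1.02 | 0.859 | 1.19 | 7.2% |
| 0.5/0.7 | 1.00 | 0.80 | 1.25 | 8.0% |
| 0.6/0.8 | 0.80 | 0.60 | 1.33 | 9.0% |
| 0.5/0.8 | 1.00 | 0.70 | 1.43 | 10.1% |
| 0.4/0.8 | 1.20 | 0.80 | 1.50 | 11.0% |
| 0.6/0.8, but T4 with T2 and T3 at 0.6 | 0.80 | 0.733 | 1.09 | 6.1% |
| Common 0.7, baseline SD 0.7 | 0.51 | 0.555 | 0.92 | 4.1% |
| Common 0.6, T4 SD 1.3 | 0.80 | 0.965 | 0.83 | 3.1% |
| Common 0.7, but T4 with T2 and T3 at 0.4 | 0.60 | 0.80 | 0.75 | 2.4% |

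Simulation (66 per group, 20,000 null trials per pattern) agreed with the formula to about 0.3 percentage points. The true standard error is √1.19 = 1.09 to √1.50 = 1.22 times the reported one in the second to sixth rows. It is √0.75 = 0.87 times in the last.

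**The written procedure, no effect at any visit** (79 per group, 20,000 runs), week-8 change declared significant:

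| Pattern | Ungated | Gate only | Gate + Bonferroni over 3 |
|---|---|---|---|
| Serial 0.7 | 7.2% | 3.5% | 2.3% |
| 0.6/0.8 | 9.0% | 4.1% | 2.9% |
| 0.5/0.8 | 10.0% | 4.9% | 3.6% |
| 0.6/0.85 | 10.8% | 5.4% | 3.9% |

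The highest values in any pattern tried were 5.6% (gate only) and 4.1% (gate plus Bonferroni over 3), both at 0.4/0.8. In the inflating patterns run at 66 per group, the interaction test itself rejected at 5.6-7.1%.

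**The written procedure, true effect at T2 only** (0.4 SD, nothing at T3). In the patterns that depart from compound symmetry the gate opens in 84-98% of trials. The false week-8 rate is then 7.2-10.4% unadjusted and 2.7-4.9% with Bonferroni over 3, against 1.6% with Bonferroni over 3 under compound symmetry.

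**Interval.** Coverage of the nominal 95% interval for the change is 92.6% (serial 0.7) and 89.7% (0.6/0.85).

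**Alternative.** Using the change's own variance, as an unstructured covariance does, the ungated contrast rejects at 4.8-5.4% in every pattern in which it was simulated.

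**The case against.** A reader might infer that the trial's primary test has a 7-11% false-positive rate, or that its standard error is simply too small. The documents support neither.

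- **Gate.** The 7-11% belongs to an ungated, unadjusted contrast, which the article does not plan. As written, the week-8 rate stays near or below nominal when no visit has an effect. This stands. However, a gate does not correct an interval, and it gives little protection once another visit has a real effect. The Bonferroni protection depends on the number of comparisons, and with a single comparison it does nothing.
- **Direction.** No covariance is given, and ungated rates ran from 2.3% to 11.0%. Treating T4 as different because it is off treatment, which the design suggests, reduces the inflation or reverses it. Entry on restricted lipid ranges (section 2.3.1) may shrink the baseline SD. With a baseline SD of 0.7 the rate was 4.1-6.6%, depending on the correlations. This stands too.
- **Which contrast.** If the post-hoc test compared groups at week 8 itself instead of the change, simulated ungated rates were about 3.4-6.8%. The stated primary outcome is the change.
- **Unseen SAP.** SPSS MIXED allows a residual structure alongside a random intercept, and a SAP may add one, which would meet the point. But the article is not silent. It names the random intercept as the device that handles the correlation, and a SAP that followed it would carry the assumption forward.
- **Simplifications.** The simulations used complete data, without the planned multiple imputation or imbalance covariates. The figures show the mechanism and its rough size; they do not forecast this trial's error rate.

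**Conclusion.** The point holds in a limited form. With independent residuals, the stated model ties the primary standard error and interval to compound symmetry, which the design gives reason to doubt. The direction of the error is unknown. Under serial decay or weaker baseline-to-follow-up correlation, the ungated, unadjusted contrast runs at about 7-11% and the interaction test at about 6-7%. Under the written gate the week-8 rate is about 3-5% with no effect anywhere, and about 2-4% with Bonferroni over three. It is about 7-10% unadjusted, or 3-5% with Bonferroni over three, if only another visit has an effect. The interval stays miscalibrated throughout. Under other plausible patterns there is little inflation, or the test is conservative and loses power. All of these figures rest on assumed correlations and complete data. This is a worthwhile, cheap improvement, not evidence that the primary test is invalid.

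**What to change.** In section 2.8.2, replace the random intercept with an unstructured within-subject covariance across the four visits (REPEATED in SPSS MIXED, with Satterthwaite degrees of freedom). Take the week-8 LDL-C contrast and its interval from that model, and use the same structure for the other four-visit outcomes. A fallback order in case of non-convergence may be added but is optional.

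The cost is one sentence, with no new data or patients and no change of software. The model estimates 4 × 5/2 = 10 covariance parameters instead of 2, a small burden with 158 patients. Intervals will be wider where the random-intercept model would have understated them.

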### Study design

2.1.

This study will conduct a prospective, multicenter, double-blind randomized controlled trial at the Second Affiliated Hospital of Hunan University of Chinese Medicine, Hunan Integrated Traditional Chinese and Western Medicine Hospital, and Chenzhou First People’s Hospital. The study has received approval from the Ethics Committee of the Second Affiliated Hospital of Hunan University of Chinese Medicine (Approval Certificate Numbers: KY-2025-023-01, [2025] No. 371, (Research) No. 2025100), and has been registered on the International Traditional Medicine Clinical Trial Registry Platform (https://itmctr.ccebtcm.org.cn/mgt/search; Registration Number: ITMCTR2025001463). This study will be reported in accordance with the Declaration of Helsinki and the Standard Protocol Items: Recommendations for Interventional Trials (SPIRIT) guidelines. We plan to recruit 158 eligible participants from August 2025 to June 2027. After signing informed consent forms, they will be randomly assigned to two groups: the infrared moxibustion group (IM group) and the sham infrared moxibustion group (Sham IM group), as detailed in Figure 1.

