### Randomization, allocation concealment, and blinding

2.2.

Central stratified randomization will be employed using SAS 9.3 (SAS Institute Inc., Cary, NC, USA) statistical software to generate random numbers. Eligible participants will be randomly assigned to the IM group and the sham IM group in a 1:1 ratio through a central randomization system. The central randomization system will be managed by independent personnel who will not be involved in participant recruitment, intervention delivery, outcome assessment, or statistical analysis to prevent selection bias. Both participants and the treating physicians will be blinded to the treatment allocation between active infrared moxibustion and sham infrared moxibustion. Throughout the data collection and analysis process, assessors and statisticians will also be blinded to the treatment allocation.

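### Randomisation is stratified, but the outcome model names no stratum or site term and its covariate rule will not select one; pre-specifying these terms, crossed with time, is a free improvement

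*Protocol article*

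**What the plan says.** - **Design.** Section 2.1 describes a "prospective, multicenter, double-blind randomized controlled trial" at three named hospitals.
- **Allocation.** Section 2.2 states: "Central stratified randomization will be employed using SAS 9.3". The ratio is 1:1. The stratification factors are not named.
- **Primary outcome.** Section 2.5.1: "The change in LDL-C from baseline to 8 weeks after intervention".
- **Model.** Section 2.8.2: "Linear mixed models will be used to analyze data from the four measurement time points". Baseline is one of those four visits, so it enters as a response. The terms follow: "The model will include group, time, and the group × time interaction as fixed effects, with the subject set as a random intercept".
- **Covariates.** The same section adds one rule: "The model will include variables that were unbalanced between groups at baseline as covariates".
- **What is tested at baseline.** Section 2.8.1 compares demographic data, the outcomes and plasma TMAO between arms at the 0.05 level. Site is not on that list.

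**The concern.** Stratified allocation removes between-stratum variation from the comparison of the arms. The analysis collects that gain only if the model also takes this variation out of the residual. Here the listed model does not, and the covariate rule works against it. The rule adds a variable when the arms differ on it, and stratification exists to stop the arms differing on its factors. The terms the design was built around are therefore those the rule is least likely to admit.

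Where an omitted factor is prognostic, the reported standard error exceeds the true sampling variation of the estimate. The intervals are then wider than the design earned, the test runs below its nominal 5% level, and some power is lost. The secondary outcomes in section 2.8.2 use the same model. How far this reaches the primary endpoint depends on whether the factor predicts change in LDL-C or only its level, so the two cases are worked separately below.

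**Working it through.** The plan gives no site-level figure and no standard error, so there is no stated number to reproduce on this point. Site effects, within-patient correlation and block size below are assumptions.

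**Step 1. Can the covariate rule select a stratification factor?** Assume site is the stratum, with three equal sites and permuted blocks of 4. In 2,000 simulated trials site was unbalanced at p < 0.05 in none (smallest p 0.98). Under unstratified randomisation the rate was 5.2%. In practice the rule never selects it.

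**Step 2. Sites differ only in LDL-C level.** A constant site difference adds the same amount to a patient's baseline and week-8 values. It is absorbed by the subject intercept and cancels from the change. Simulation of the four-visit model used 158 patients, 6,000 runs per setting and correlation 0.6. The SD was 0.477, the pooled value from section 2.7: √((0.52² + 0.43²)/2). With site level SD from 0 to 0.25 mmol/L, the SE of the week-8 change contrast was 0.068 with and without a site term, and rejection under the null was about 0.05. There is no excess.

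**Step 3. Sites differ in change.** Assume three equal sites, within-site SD of change 0.45 mmol/L, and site mean changes spread evenly over 0.2, 0.4 or 0.6 mmol/L. The between-site variance is V = 2d²/3, with d half the spread:

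- d = 0.1: V = 0.00667
- d = 0.2: V = 0.02667
- d = 0.3: V = 0.06

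*Simple comparison of week-8 changes.* The SE ratio is √(1 + V/0.45²) = 1.016, 1.064 and 1.139.

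*Planned four-visit model.* The residual variance is pooled over visits, so only part of V enters it. With compound symmetry the residual variance is 0.45²/2 = 0.10125. Let the site effect follow the profile f over the four visits. The pooled residual gains V·k, where k = Σ(f − mean f)²/3, and the SE ratio is √(1 + kV/0.10125).

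| Profile f | k | Spread 0.2 | Spread 0.4 | Spread 0.6 |
|---|---|---|---|---|
| Full from week 4 (0, 1, 1, 1) | 0.250 | 1.008 | 1.032 | 1.071 |
| Half at week 4 (0, 0.5, 1, 1) | 0.229 | 1.007 | 1.030 | 1.066 |

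A separate simulation of the planned model (132 completers = 2 × 66, 8,000 runs, three time profiles) gave about 1%, 3% and 6–8%. Type I error was about 4.7%, 4.5% and 3.4–4.0%.

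The 158-patient simulation agrees. With site SD of change 0.10 and 0.20, the SE was 0.0687 and 0.0715 without a site term, against 0.0678 with site × time: about 1% and 5% too large.

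**Step 4. Which term helps?** In those runs a site main effect left the SE of the change contrast at 0.0687 and 0.0715. Only site × time lowered it.

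**Step 5. Contrasts on levels.** The relevant variance at one visit is 0.477² = 0.2276. With site level SD 0.15 and 0.25 the ratio is √(1 + 0.0225/0.2276) = 1.048 and √(1 + 0.0625/0.2276) = 1.129. The simulation gave 0.0796 against 0.0759 and 0.0856 against 0.0758, which is 5% and 13% too wide. Rejection under the null was 0.038 and 0.027.

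**Step 6. Power on the primary contrast.** For a test with 95% power the noncentrality is 1.96 + 1.645 = 3.605. If the reported SE is r times the true one, power is Φ(3.605 − 1.96r): 94.8% at r = 1.01, 94.4% at 1.03 and 93.2% at 1.08.

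**The case against.** **The documents do not show that site matters for change in LDL-C.** Sections 2.4.1 and 2.4.2 describe one chamber model with a fixed setting and duration, and the same lifestyle advice for both arms. A reader might infer that the LDL-C intervals are certainly too wide. The text does not support that: the endpoint is a change, baseline is a modelled visit, and stable level differences cancel. This objection stands and makes the point conditional.

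**The strata are not said to be the hospitals.** A reader might join the multicentre design to the stratified allocation and assume so. That is a guess, and the simulations share it. It stands, and the fix is worded to cover either case.

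**The larger percentages belong to another analysis.** The 2%, 6% and 14% from a plain comparison of week-8 changes might be taken as the cost of the planned model. That model pools residual variance over visits and shows roughly half. The widest scenario, 0.6 mmol/L between sites, is also close to the whole 0.69 mmol/L group difference in section 2.7. This stands.

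**An article condenses, and stratification factors are often settled in the analysis plan.** This explains the unnamed strata, which are not criticised here. It does not cover the covariate rule, which is stated and would leave the stratification factors out if followed as written.

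**Conclusion.** The mismatch is real and minor. Randomisation is stratified, the model as listed ignores this, and the imbalance rule will not put it right. For the primary LDL-C contrast the standard error is too large only if stratum or site predicts change. The excess is then about 1%, 3% and 6–8% at assumed spreads of 0.2, 0.4 and 0.6 mmol/L (three equal sites, SD of change 0.45), with a power loss of at most about two points from 95%. If sites differ only in level, the excess is nil. Group main effects, and post-hoc tests if they compare arms within a visit, are more exposed: about 5–13% at an assumed site level SD of 0.15–0.25 mmol/L.

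The direction is conservative throughout, so this is no threat to the validity of a positive result. It is a free improvement: analysing by the groups within which the trial already randomises.

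**What to change.** In section 2.8.2, state that the model includes the randomisation stratification factors, listed by name, and study site if it is not one of them. Enter them as fixed effects together with their interaction with time, regardless of any baseline test. The interaction is needed, because a main effect alone leaves the week-8 change contrast as it is.

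The cost is one sentence and a few degrees of freedom. For three sites over four visits it is 2 main-effect and 2 × 3 = 6 interaction parameters, 8 in all, with more if there are further strata. No new data are required.

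### The baseline correction in section 2.8.2 cannot act on the primary week-8 LDL-C change, and that change is estimated less precisely than a baseline-adjusted analysis would allow

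*Protocol article*

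**What the plan says.** - **Primary outcome (section 2.5.1):** "The change in LDL-C from baseline to 8 weeks after intervention".
- **Visits (section 2.5):** four assessments, of which baseline (T1) is the first, then weeks 4 and 8 of treatment and four weeks after treatment ends.
- **Response data (section 2.8.2):** "Linear mixed models will be used to analyze data from the four measurement time points". Baseline is therefore a response row.
- **Model terms (section 2.8.2):** "The model will include group, time, and the group × time interaction as fixed effects, with the subject set as a random intercept". No covariate × time term is stated, and the arms are not constrained to a common baseline mean.
- **Covariates (section 2.8.2):** "The model will include variables that were unbalanced between groups at baseline as covariates to correct for the impact of baseline differences". The sentence goes on to say that this applies to the treatment effect estimates.
- **Missing data (section 2.8.2):** multiple imputation, so each analysed data set is complete.
- **Baseline tests (section 2.8.1):** "we will compare differences in each outcome between the two groups at baseline", with two-sided tests at 0.05.
- **Randomisation (section 2.2):** "Central stratified randomization will be employed". The stratification factors are not named.

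**The concern.** When baseline is a response and each patient has a random intercept, the effect on change is a comparison within patients. A covariate with one value per patient shifts all four of that patient's expected values equally, so it cancels from any difference between visits. The article names these covariates as the means of protecting the treatment effect estimates from baseline differences. On its primary outcome they cannot do so.

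Two things are at stake. A chance LDL-C difference at entry would be handled by plain subtraction, although readers would be told that it had been corrected. And the precision available from regressing on baseline LDL-C, which is already measured, would be given up.

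**Working it through.** **1. Algebra.** Write y_ij = μ_j + γ_j·g_i + β·x_i + b_i + e_ij, with x_i constant over visits j. For one patient, the week-8 minus baseline difference is (μ_8 − μ_0) + (γ_8 − γ_0)·g_i + (e_i8 − e_i0). Both β·x_i and b_i drop out. With complete data, the estimate of γ_8 − γ_0 is the between-arm difference in mean change, and its standard error comes from within-patient residual variance, to which x does not contribute.

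**2. Numerical check.** One simulated data set: 79 per arm, four visits, intercept correlation 0.6, and age made prognostic and unbalanced by 0.3 SD. The raw difference in mean change is −0.15895.

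| Model | Week-8 estimate | SE |
|---|---|---|
| As in 2.8.2, no covariate | −0.15895 | 0.0688 |
| plus age | −0.15895 | 0.0688 |
| plus age and baseline LDL-C | −0.15895 | 0.0688 |
| Regression of week 8 on group and baseline LDL-C | −0.1651 | 0.0593 |
| the same, plus age | −0.1857 | 0.0594 |

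The first three rows agree to at least 10 decimals for the estimate and 6 for the SE.

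**3. What is left unadjusted.** If the arms differ by Δ at baseline and the regression slope on baseline is b, the change estimate minus the adjusted estimate is −(1 − b)·Δ. In the simulated data Δ = −0.01784 and the gap is −0.15895 − (−0.16512) = 0.00617, so 1 − b ≈ 0.35 and b ≈ 0.65. The gap grows in proportion to Δ.

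**4. Precision.** Let σ be the LDL-C SD, taken as equal at baseline and week 8, ρ the correlation between the two, and n the number per arm.

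- Change score: SE = σ·√(2(1 − ρ))·√(2/n)
- Adjusted: SE = σ·√(1 − ρ²)·√(2/n)
- Variance ratio: (1 − ρ²) / (2(1 − ρ)) = (1 + ρ)/2

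Inputs: σ = √((0.52² + 0.43²)/2) = 0.477 mmol/L from the SDs in section 2.7; n = 66 from section 2.7; ρ assumed. For power, a contrast with true 95% power has a standardised effect of 1.960 + 1.645 = 3.605. After adjustment, power is Φ(3.605/√ratio − 1.960).

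| Assumed ρ | Variance ratio | SE, change | SE, adjusted | 95% power becomes |
|---|---|---|---|---|
| 0.5 | 0.75 | 0.0830 | 0.0719 | 98.6% |
| 0.6 | 0.80 | 0.0743 | 0.0664 | 98.1% |
| 0.7 | 0.85 | 0.0643 | 0.0593 | 97.4% |

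Over a wider range the variance saving is 35% at ρ = 0.3 and 5% at ρ = 0.9.

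The 95% is the power stated in section 2.7, taken here as a starting point. The stated 66 per group does not follow from the means and SDs in that section, which give 13 (normal approximation) or 14 (t-test). That is a separate matter and affects nothing in steps 1 to 3 or the variance ratios.

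**5. Covariance (secondary).** A random intercept alone imposes one correlation on all pairs of visits. Suppose instead that correlation decays as 0.8 per four weeks. The average over the six pairs is (3×0.8 + 2×0.64 + 0.512)/6 = 0.699, while the baseline-to-week-8 correlation is 0.64. The SE ratio is √((1 − 0.699)/(1 − 0.64)) ≈ 0.915, and the two-sided error rate is 2Φ(−1.960 × 0.915) ≈ 7.3%. If a quarter of the variance is independent visit noise, the rate is 5.7% to 6.2% for decay of 0.7 to 0.9; if half is, 5.3% to 5.7%. With constant correlation there is no inflation.

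**The case against.** **The covariates do something.** Section 2.8.2 also speaks of group effects and of Bonferroni post-hoc tests, whose contrasts it does not define. Covariates do move level contrasts: in the simulated data, adding age moved the time-averaged group effect from −0.123 to −0.163. This stands, so it would be wrong to infer that the covariates are useless throughout. It does not rescue the primary outcome, which is defined as a change. Nor would baseline LDL-C be well handled in a level contrast: with baseline also a response, its slope under equal correlation averages 1, ρ, ρ and ρ, or (1 + 3ρ)/4, which is 0.70 instead of 0.60 at ρ = 0.6.

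**The planned contrast is not biased.** A reader might infer that a baseline imbalance makes the primary result invalid. Under randomisation the change contrast is unbiased, and it already uses baseline by subtraction. The loss is in precision and in how one observed imbalance is handled.

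**The invariance needs complete data.** True, but imputation is planned. Even without it, with 20% of the simulated patients missing weeks 8 and 12, the estimate moved only from −0.115 to −0.118 with age and −0.120 with age and baseline LDL-C.

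**Choice of covariates by imbalance and the absent stratification term.** A reader might infer that these distort the primary test. Within the model as written they cannot, because they too are constant over time. Section 2.8.1 does not say that its tests select the covariates, section 2.8.2 does not define imbalance, and the strata may be listed in a fuller plan. These points matter once the model is repaired.

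**Error rate.** That the primary test exceeds 5% is likewise not established. It depends on a decay pattern that the article does not give, and a residual covariance structure may be specified elsewhere.

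**Conclusion.** The point holds for the primary outcome. As written, the correction promised in section 2.8.2 cannot change the week-8 LDL-C change estimate or its standard error. With complete data and main-effect covariates this follows from algebra and needs no assumption about the data.

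The cost is one of efficiency and of a stated safeguard that does not operate; it is not bias. The variance is 15% to 25% higher than the saving from adjustment would leave it only in the sense that adjustment removes 15% to 25% of it, at ρ from 0.7 to 0.5. That rests on an assumed ρ and on equal variances at the two visits. If the unadjusted contrast truly has 95% power, the gain is about 2.4 to 3.6 percentage points. The possible error rate of about 7% is an upper figure under pure serial decay and is secondary. The article should be changed, but the flaw does not undermine the trial.

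**What to change.** Replace the model paragraph in section 2.8.2 with wording such as: LDL-C at T2, T3 and T4 is the response; fixed effects are group, visit, group × visit, baseline LDL-C and baseline LDL-C × visit, included whatever balance is observed; the primary estimate is the group difference at T3. An equivalent route keeps baseline as a response and constrains the arms to a common baseline mean. Use the same form for the other outcomes measured at all four visits.

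Present baseline data descriptively in section 2.8.1, and do not choose covariates by observed imbalance.

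As secondary changes, include the randomisation stratification factor or factors and use an unstructured within-subject covariance, so that the standard error does not depend on equal correlation between visits.

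The cost is analysis wording and a few more covariance parameters, which is small with 158 patients planned. No new data are needed: baseline LDL-C is already scheduled, and the strata are known to the central randomisation system.
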